#### iii) High-intensity Intervention

Patients who have high levels of distress as measured on the HADS (scores of 22 or greater) have needs beyond the training of the health professionals participating in this study and require a high-intensity Intervention. All patients in this category will be referred for Specialised Treatment (high-intensity Intervention) with an appropriately qualified practitioner via a pre-defined clinical pathway at the respective site.

#### iv) Usual Care

Patients with *no *current distress (DT Score < 4) and *no *risk factors (on Psychosocial Checklist) will not receive any additional information or psychosocial support related to coping with cancer beyond the normal clinical practice at the site where they are receiving cancer care. They will continue to participate in follow-up or cancer-specific treatment as usual. They will not have contact with the trained health professionals at that site other than in the usual course of clinical care.

### Participants

#### Health professionals

Health professionals from the disciplines of nursing, occupational therapy, speech pathology, nutrition and dietetics, physiotherapy or radiation therapy will be eligible to participate in training if they: (1) have at least 12 months' clinical experience in oncology (2) are currently engaged in patient contact (minimum of 6 hours per week) (3) have a commitment to undertake the necessary training and (4) are working in a setting in which they can deliver the Intervention. Health professionals who meet the selection criteria will be offered entry into the study by the Investigators and will complete baseline measures before receiving a self-directed training manual and participating in a day-long skills development session. The core elements of the training will be (1) Supportive/expressive - encouraging expression of emotions; validating the individual's experiences; empathic listening, and provision of information (2) Cognitive-behavioural - teaching skills in problem-solving; identifying and challenging automatic thoughts; reframing; relaxation training and guided imagery (3) Dignity-conserving - encouraging reflection on themes of coherence, isolation, hope, helplessness, purpose and courage, as well as practical needs. This training will be completed over a period of 10 weeks. Psychologists, social workers and psychiatrists will not be eligible to participate as (1) it is considered that their core skills encompass the material included in the training, and (2) patients may be referred to these professionals as part of the intervention, for example a patient may be referred to a social worker because of financial concerns (as per Table 3). The number of health professionals to be trained at each site will vary depending on when that site is randomised. We aim to train sufficient numbers of health professionals so that no health professional is required to deliver the Intervention to more than 2 patients per Epoch (10-week cycle depicted in Table 1).

#### Patients

Inclusion criteria are: (1) aged 18 years or over (2) consecutive patients attending outpatient oncology clinics at each site (3) currently receiving active treatment for cancer OR have completed active treatment within the previous 2 months OR have been diagnosed with recurrent/advanced cancer within the previous 2 months. Exclusion criteria are: (1) inability to speak and read English, (2) receiving current specialised psychological treatment from a psychologist, psychiatrist, or other trained counsellor, (3) currently taking antidepressant medication, (4) health status precludes ability to complete questionnaires and participate in up to four psychosocial Intervention sessions and follow-up at 10 weeks, and (5) recruited in any previous Epoch of this study (that is, patients can only participate during one Epoch).

We will recruit 20 patients per site per Epoch (with the exception of the Training Epochs during which no patients will be recruited) with a total sample size of 600 patients. No patient who has been recruited in a previous Epoch will be eligible to participate in subsequent Epochs. Primary outcome measure is change in HADS score over ten weeks from enrolment to follow-up. Estimates of HADS in similar populations [35] are a mean of 17.8 with SD = 9.0, with a 10%-15% difference in mean change-scores assumed to be clinically significant. To detect this difference, with power = 80%, in a before-after design assuming a correlation 0.5 within patient over time, about 200 patients in each group are needed (Stata IC, version 10). Patients will be clustered by clinic, but we have no data on which to estimate intraclass correlation for the HADS scores; so will assume a design effect of deff = 1.5 to accommodate clustering, and hence we will require 600 patients in all; across five clinics, so we will seek to enrol 120 patients per site.

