### Statistical analyes

#### Quantitative analysis

We will compute and compare the average change in HADS scores among patients enrolling during Intervention Epochs with scores of patients enrolling during Control Epochs. The strength of the stepped-wedge design is that we will be able to account for systematic differences between sites and times during the trial, and also for case-mix differences between patients.

We will use a patient-level hierarchical analysis model to accommodate these potentially confounding factors. With this model, we can adjust for case-mix differences between sites, as well as allow for specific site characteristics (other than presence/absence of the Intervention). A generalised estimating equation (GEE) linear or logistic model will be implemented [28] to estimate the effect of the Intervention on the patients' change in HADS scores and the prevalence of depression "caseness" at each site. Stata Version 10 (StataCorp, 2008) will be used for all statistical analyses.

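### Baseline HADS is not named as a covariate in the primary model of HADS change; naming it would cut the variance by 25% at the plan's own correlation

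*Protocol article*

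**What the plan says.** Under Patients, the protocol article defines the endpoint: "Primary outcome measure is change in HADS score over ten weeks from enrolment to follow-up". The sample size paragraph there takes "a mean of 17.8 with SD = 9.0" for HADS and sizes the trial "assuming a correlation 0.5 within patient over time".

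The Quantitative analysis section first promises a comparison of average HADS change between patients enrolled in Intervention and in Control Epochs. It then describes a patient-level hierarchical model, implemented by GEE, "to estimate the effect of the Intervention on the patients' change in HADS scores", with a logistic version for the prevalence of caseness. It says that the design lets the analysis account for site, time and case-mix differences. Case-mix is not defined, and baseline HADS is neither named nor excluded.

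Patient assessment instruments lists HADS among the measures taken at baseline and at 10 weeks. Study Integrity states that patients are not randomised and that consecutive attenders are screened and enrolled if eligible and consenting. Under Patients, each person may take part in one Epoch only.

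**The concern.** Subtracting the baseline is an efficient use of it only when the correlation between the two measurements is high. At 0.5 the subtraction adds as much noise as it removes, so the change score is no more precise than follow-up HADS alone. Entering baseline HADS as a covariate uses the same data better.

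The second issue is comparability. The two conditions consist of different people, enrolled at different times, without individual randomisation. If their baseline HADS differs after site and time are accounted for, regression to the mean makes the higher group appear to improve more, and a change score with no baseline covariate carries that into the treatment contrast.

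At stake is precision in a five-site stepped-wedge trial, where adjusting for site and time already uses up much of the information, and protection against a baseline difference if one occurs.

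**Working it through.** **Inputs.** From the Patients section: SD 9.0, mean 17.8, correlation 0.5, power 80%, a difference of 10% to 15%, about 200 per group, design effect 1.5. Assumptions: two-sided alpha of 0.05 (not stated); the percentage is taken of the mean of 17.8 (its base is not stated), giving 1.78 to 2.67 points; equal SD at baseline and follow-up.

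**1. The plan's own figure.**
- SD of change = 9.0 × √(2 × (1 − 0.5)) = 9.0.
- n per group = 2 × (1.960 + 0.842)² × 81 / d² ≈ 1271.5 / d².
- d = 1.78 (10%) gives 402; d = 2.53 (14.2%) gives 200; d = 2.67 (15%) gives 179.
- At 14.2%, the total is 2 × 200 × 1.5 = 600.

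So "about 200 patients in each group are needed" is reproduced with the change-score variance, at a difference inside the stated range.

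**2. Variance under the two analyses.**
- Change score: 2 × 81 × (1 − 0.5) = 81, the same as follow-up HADS alone.
- Baseline-adjusted: 81 × (1 − 0.5²) = 60.75.
- Ratio 60.75 / 81 = 0.75. The SE ratio is √0.75 = 0.866, a 13% reduction. Since 1 / 0.75 = 1.33, this is worth 33% more patients.
- In general the saving is 1 − (1 − ρ²) / (2(1 − ρ)) = (1 − ρ) / 2: 35% at 0.3, 25% at 0.5, 20% at 0.6, 10% at 0.8.

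**3. What that means at 200 effective patients per group (simple two-group comparison).**

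| Difference | Power, change only | Power, baseline-adjusted |
|---|---|---|
| 1.78 (10%) | 0.51 | 0.63 |
| 2.53 (14.2%) | 0.80 | 0.90 |
| 2.67 (15%) | 0.84 | 0.93 |

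The difference detectable with 80% power falls from 2.52 to 2.18 points.

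**4. The same comparison in the layout of Table 1.** There are 30 recruiting site-by-Epoch cells, 15 Control and 15 Intervention, with 20 patients each. With fixed site and Epoch effects and independent patient errors, the SE of the Intervention effect is 1.63 points for change scores and 1.41 with baseline adjustment. At 2.67 points, power is 0.37 against 0.47.

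**5. Sensitivity to baseline imbalance.** With a regression slope of 0.5, a residual baseline difference of 1 point moves the unadjusted change contrast by (1 − 0.5) × 1 = 0.5 point. That is 0.5 / 1.78 = 28% of the smaller target and 0.5 / 2.67 = 19% of the larger. The chance SE of the baseline difference is 9.0 × √(2/300) = 0.73 point for a plain 300 v 300 comparison, 0.73 × √1.5 = 0.90 with the design effect, and 1.63 in the site-and-Epoch model of step 4. The document gives no figure for the imbalance to expect.

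**The case against.** The strongest reply is that the article does not plan an unadjusted analysis. It describes a patient-level model with case-mix adjustment, and baseline severity is an obvious case-mix variable. Full covariate lists are commonly left to an analysis plan, which is not shown. A linear model of change with baseline HADS as a covariate gives the same Intervention effect and SE as a model of 10-week HADS with that covariate, so the endpoint definition causes no loss. All of this stands. A reader might infer that the plan commits to raw change, but the text does not say so. What remains is that the article fixes the modelled quantity as change and leaves open the one covariate that matters most to it.

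A reader might also infer that imbalance is likely because recruiters know each site's condition. The article does not say who enrols patients or what they know. It says only that patients and the delivering health professionals cannot be blinded, and it sets consecutive screening and documented enrolment against selection. Lack of blinding does not by itself produce regression to the mean.

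Nor is baseline adjustment always the less biased choice in non-randomised groups. Where groups differ for stable reasons, it can under-correct and the change score can be right. The precision argument does not depend on this, but it is a reason not to claim that adjustment removes all bias.

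**Conclusion.** The point holds as a worthwhile improvement. Not naming baseline HADS risks giving up 25% of the variance (13% of the SE) at the plan's own correlation of 0.5. The size rests on that assumed correlation, on equal SDs at the two times and, for the Table 1 figures, on independent patient errors. At a correlation of 0.8 the saving would be only 10%.

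The bias is a conditional risk: about 0.5 point per point of residual baseline difference if baseline is left out. Chance imbalance is already reflected in the change-score SE; a systematic bias would need differential enrolment or case-mix drift not captured by site and time, and the document shows neither.

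It is tempting to read the sample size as evidence that baseline adjustment was assumed, since 193 per group results from adjustment at 12.5% of the mean. That inference fails: change scores at about 14% of the mean also give about 200, and the midpoint of the range is not the plan's choice. The point does not make the total of 600 wrong.

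**What to change.** In the Quantitative analysis section, state that the primary linear model of change in HADS (or, equivalently, of 10-week HADS) includes baseline HADS as a covariate together with site, Epoch and Intervention. State that the logistic model includes baseline HADS or baseline caseness; the first hypothesis concerns a reduction in caseness, while the analysis section models its prevalence.

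The cost is one or two sentences and one model parameter. The baseline value is already collected in every patient. Neither the endpoint definition nor the sample size needs to change for this point.

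### One sample size is given for a 10%-15% difference, but about 200 per group has 80% power only towards the upper part of that range, not at 10%

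*Protocol article*

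**What the plan says.** The sample-size paragraph is in the protocol article under Participants, Patients. It fixes the outcome: "Primary outcome measure is change in HADS score over ten weeks from enrolment to follow-up". It gives the planning values: "Estimates of HADS in similar populations [35] are a mean of 17.8 with SD = 9.0". The target follows as a range rather than a single value: "with a 10%-15% difference in mean change-scores assumed to be clinically significant". The paragraph then states the result: "To detect this difference, with power = 80%, in a before-after design assuming a correlation 0.5 within patient over time, about 200 patients", a figure that applies to each of the two groups. A design effect of 1.5 for clustering raises the total to 600, spread "across five clinics, so we will seek to enrol 120 patients per site".

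The paragraph does not state the significance level or whether the test is one- or two-sided. It does not say which point of the 10%-15% range was used, or whether the calculation adjusts for baseline HADS.

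**The concern.** The required sample size varies with the inverse square of the difference to be detected. Between 10% and 15% it changes by a factor of (15/10)² = 2.25, so one number cannot give 80% power at both ends. If 200 per group suits the upper part of the range, the lower end is underpowered, although the article also calls that difference clinically significant.

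This is the only power justification shown for the primary outcome. A null result could be read as evidence against a 10% effect that the trial had limited power to detect.

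**Working it through.** **Inputs from the Patients section.** Mean 17.8, SD 9.0, within-patient correlation 0.5, power 80%, about 200 per group, design effect 1.5.

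**Assumptions.**
- Two-sided alpha is 0.05; one-sided 0.05 is tried as a variant.
- The percentages are taken of 17.8, the only base the article gives: 10% = 1.78, 12.5% = 2.225 and 15% = 2.67 points.
- The design effect of 1.5 exactly offsets clustering, so 200 per group is the effective number.

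**Variance.**
- Change score: 2 × 81 × (1 − 0.5) = 81, SD 9.0.
- Baseline-adjusted: 81 × (1 − 0.5²) = 60.75, SD 7.79.

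**Can the plan's own figure be reproduced?** n per group = 2 × (1.96 + 0.8416)² × variance / difference².

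| Difference | Change score | Baseline-adjusted |
|---|---|---|
| 1.78 (10%) | 401.3, so 402 | 301.0, so 301 |
| 2.225 (12.5%) | 256.8, so 257 | 192.6, so 193 |
| 2.67 (15%) | 178.4, so 179 | 133.8, so 134 |

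Neither end of the range gives 200. Several unstated choices come close:
- 14.2%, unadjusted, two-sided: 200
- 12.5%, adjusted, two-sided: 193
- 12.5%, unadjusted, one-sided: 203
- 15%, unadjusted, two-sided, with 10% dropout: 179/0.9 = 199
- a single-group before-after test at 10%: (1.96 + 0.8416)² × 81 / 1.78² = 200.7

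**Power with 200 per group.** The standard error is 9.0 × √(2/200) = 0.90 unadjusted and 7.79 × √(2/200) = 0.779 adjusted. Power = Φ(difference/SE − 1.96), with 1.645 in place of 1.96 for the one-sided test.

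| Difference | Change score | Baseline-adjusted |
|---|---|---|
| 1.78 (10%) | 51% | 63% |
| 2.225 (12.5%) | 70% | 82% |
| 2.67 (15%) | 84% | 93% |

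One-sided at 10%, power is 63% unadjusted and 74% adjusted. No two-group variant tried reaches 80% at 10%.

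**Smallest difference with 80% power at 200 per group (two-sided).**
- Unadjusted: 2.8016 × 0.90 = 2.52 points; 2.52/17.8 = 14.2%.
- Adjusted: 2.8016 × 0.779 = 2.18 points; 2.18/17.8 = 12.3%.

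**Totals with the design effect (two-sided, unadjusted).** At 10%, 402 × 2 × 1.5 = 1,206. At 15%, 179 × 2 × 1.5 = 537. The plan has 600.

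**Follow-up (secondary).** 200 × 2 × 1.5 = 600 and 600/5 = 120 per site, so the stated arithmetic has no explicit margin for a missing 10-week HADS. With an assumed 10% or 20% loss, 180 or 160 per group remain. Unadjusted power at 15% is then 80% or 76%, and at 10% it is 47% or 42%.

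**The case against.** **The figure is not wrong for the whole range.** A reader might infer that 200 per group fails throughout 10%-15%. It does not. It is adequate near 15% on either analysis, and at 12.5% with baseline adjustment. This objection stands and limits the point to the lower part of the range.

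**The figures of about 401 per group and 51% power are the least favourable variant.** They rest on an unstated two-sided alpha of 0.05 and an unadjusted change score. The Quantitative analysis section plans a patient-level model with case-mix adjustment. It does not name baseline HADS as a covariate, but an adjusted analysis is plausible. The fair statement at 10% is therefore a range: 51% to 74% power, and 402 down to 238 per group (the last one-sided and adjusted). This stands too, but the whole range lies below 80%.

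**The fault may be an unstated choice rather than an arithmetic slip.** The midpoint with baseline adjustment gives 193, which fits a rounded 200. The single-group formula at 10% also gives about 200, and a reader might infer that a one-sample number was mistaken for a per-group number. The article does not show how 200 was reached, so neither origin can be asserted.

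**The trial enrols 300 per group, not 200.** The article assigns that increase to clustering. If all 300 were nevertheless counted as independent, two-sided power at 10% would be 68% unadjusted and 79.9% adjusted; only the one-sided tests with adjustment would clear 80% (88%). This is no rescue unless clustering is ignored.

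**Attrition and wording.** A reader might infer that every enrolled patient must return. That does not follow at 15%, where about 10% loss still leaves 80% unadjusted, and a condensed article may leave a retention allowance to the full protocol. Read literally, the percentage is of a mean change that is never given. The only base in the sentence is 17.8, so naming it is a clarification.

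**Conclusion.** The concern holds in limited form: the stated 80% power is not met across the article's own range. At 10%, 200 per group gives 51% power unadjusted and 63% adjusted (two-sided), rising to at most 74% in the most favourable two-group variant tried. Power of 80% begins at 14.2% unadjusted or 12.3% adjusted.

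The result rests on percentages of 17.8, SD 9.0, correlation 0.5, an assumed alpha of 0.05, and a design effect of 1.5 that fully absorbs clustering. The shortfall at 10% does not depend on the choice of sidedness or adjustment, but its size does. The documents do not support saying that 200 is inadequate throughout the range, or that a particular formula error produced it. The lack of an explicit follow-up margin is secondary.

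**What to change.** In the Patients section:

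1. Name one target difference in HADS points, and give it as a percentage of the baseline mean.
2. State alpha, sidedness, and whether the calculation is for an unadjusted change score or a baseline-adjusted comparison.
3. Report power at 1.78 and 2.67 points separately, and do not claim 80% power for the 10% difference.
4. Give these powers at the number expected to complete the 10-week HADS rather than the number enrolled, with the assumed loss stated.

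The cost is rewording and a short recalculation. No extra patients are needed, and the design, outcome and analysis do not change.

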### Intervention

This study comprises two discrete components:

a) Training of health professionals who will deliver the psychosocial Intervention

b) Delivery of the psychosocial Intervention by the trained health professionals.

The design for this randomised study is a stepped-wedge cluster design, a type of crossover design in which different clusters (the clinical sites) cross over in one direction only, from Control to Training then Intervention [28]. At the conclusion of the study, all sites will have received Training and be providing the Intervention [29] delivered by health professionals who have received training at that site as depicted in Table 1.

**Table 1 T1:** Stepped wedge design.

	Epoch 1	Epoch 2	Epoch 3	Epoch 4	Epoch 5	Epoch 6	Epoch 7
Site 1	Control	TRAINING	**Intervention**	**Intervention**	**Intervention**	**Intervention**	**Intervention**

Site 2	Control	Control	TRAINING	**Intervention**	**Intervention**	**Intervention**	**Intervention**

Site 3	Control	Control	Control	TRAINING	**Intervention**	**Intervention**	**Intervention**

Site 4	Control	Control	Control	Control	TRAINING	**Intervention**	**Intervention**

Site 5	Control	Control	Control	Control	Control	TRAINING	**Intervention**

Week	1	10	20	30	40	50	60

The Intervention is sequentially rolled-out across sites in random order over a number of time periods (Epochs).

The nature of the Intervention will be *tailored to the level of need of the patient*, eligible patients receiving a "low-intensity" or "medium-intensity" Intervention, allocated according to the Algorithm depicted in Table 2.

**Table 2 T2:** Algorithm for patient allocation to Intervention

DT^1 ^score <4		DT^1 ^score 4 or greater		
No risk factors	+ risk factors^2^ HADS^3 ^< 8	+/- risk factors^2^ HADS^3 ^< 8	+/- risk factors^2^ HADS^3 ^8-21	+/- risk factors^2^ HADS^3 ^22 or greater

Usual care	**Low-intensity Intervention** Patient self-directed resource suite only		**Medium-** **intensity** **Intervention** Tailored psychosocial Intervention delivered by trained Health Professional	Specialised Treatment with an appropriately qualified practitioner via a pre-defined clinical pathway

DT^1^: Distress Thermometer

Risk Factors^2^: Risk factors as identified in the National Breast and Ovarian Cancer Centre Psychosocial Checklist (PSCL)

HADS^3^: Hospital Anxiety and Depression Scale

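### The 1.5 design effect allows for clustering but not for the stepped-wedge time adjustment, so 600 patients give about 34–51% power, not 80%

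*Protocol article*

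**What the plan says.** The sample-size paragraph (Protocol article, Participants, Patients) takes HADS to have "a mean of 17.8 with SD = 9.0", "with a 10%-15% difference in mean change-scores assumed to be clinically significant". The method is described as "To detect this difference, with power = 80%, in a before-after design assuming a correlation 0.5 within patient over time", and the result is that "about 200 patients in each group are needed (Stata IC, version 10"). With no data on the intraclass correlation (ICC), the authors write: "so will assume a design effect of deff = 1.5 to accommodate clustering, and hence we will require 600 patients in all".

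The design (Intervention section, Table 1) has five sites and seven epochs. Sites "cross over in one direction only, from Control to Training then Intervention", one site per step. Recruitment is 20 patients per site per epoch, "with the exception of the Training Epochs during which no patients will be recruited", and each patient takes part in one epoch only.

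The Quantitative analysis section gives the strength of the design as being that "we will be able to account for systematic differences between sites and times during the trial", using a patient-level hierarchical model implemented by GEE.

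**The concern.** The sample size and the analysis belong to different designs. A before-after comparison inflated for clustering assumes that all 300 Control and 300 Intervention patients inform the contrast directly. In a stepped wedge the Intervention becomes more common as calendar time passes, so adjusting for time removes much of the information about the Intervention. This loss is separate from clustering and is present even when the ICC is zero. Nothing in the calculation uses the number of epochs, the order of crossover or the empty Training cells.

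At stake is the power claim for the primary outcome. If true power is nearer 40% than 80%, a real effect of the planned size would more often be missed than found, and a null result could be taken as evidence against an Intervention that the trial could not have assessed.

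**Working it through.** **Inputs from the protocol.** HADS mean 17.8, SD 9.0; within-patient correlation 0.5; power 80%; difference 10–15%; five sites, seven epochs, 20 patients per recruiting cell.

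**Assumptions not in the protocol.** Two-sided 5% test (alpha is not stated); 10–15% read as a share of 17.8, that is 1.78 to 2.67 points; ICC from 0 to 0.10, constant over time within a site; no dropout; normal reference distribution.

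**1. The plan's own figure.**
- SD of change = 9.0 × √(2 × (1 − 0.5)) = 9.0.
- n per group = 2 × 81 × (1.96 + 0.8416)² / d². This gives 179 at d = 2.67 and 402 at d = 1.78.
- With 200 per group, the difference detectable with 80% power is 2.8016 × √(2 × 81/200) = 2.52 points (14.2% of 17.8).
- 2 × 200 × 1.5 = 600, and 30 recruiting cells × 20 = 600.

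The stated figure reproduces, near the upper end of the effect range. The multiplication is not in error.

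**2. Where the treatment contrast comes from.** Site-cells by epoch in Table 1:

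| Epoch | Control | Training (empty) | Intervention |
|---|---|---|---|
| 1 | 5 | 0 | 0 |
| 2 | 4 | 1 | 0 |
| 3 | 3 | 1 | 1 |
| 4 | 2 | 1 | 2 |
| 5 | 1 | 1 | 3 |
| 6 | 0 | 1 | 4 |
| 7 | 0 | 0 | 5 |

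Only Epochs 3 to 5 contain both conditions: 12 cells, 240 patients. The other 360 have no concurrent comparator.

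**3. Variance at ICC 0, adjusting for epoch.** Each mixed epoch contributes information n₁n₂/(n₁ + n₂):
- Epoch 3: 60 × 20/80 = 15
- Epoch 4: 40 × 40/80 = 20
- Epoch 5: 20 × 60/80 = 15

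Variance = 81/(15 + 20 + 15) = 1.62. For 300 v 300 it is 81 × (1/300 + 1/300) = 0.54. The ratio is 1.62/0.54 = 3.0, and no ICC has been assumed to reach it.

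**4. Other cases.** Generalised-least-squares variance of the treatment term on the 30 cells, with seven epoch effects. Power = Φ(d/SE − 1.96); detectable difference = 2.8016 × SE.

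| Site model | SE | Design effect | Power, 2.52 | Power, 2.67 (15%) | Power, 1.78 (10%) | Detectable with 80% power |
|---|---|---|---|---|---|---|
| ICC 0 | 1.273 | 3.00 | 51% | 56% | 29% | 3.6 |
| ICC 0.01 | 1.425 | 3.76 | 42% | 47% | 24% | 4.0 |
| ICC 0.05 | 1.522 | 4.29 | 38% | 42% | 21% | 4.3 |
| ICC 0.10 | 1.513 | 4.24 | 38% | 42% | 22% | 4.2 |
| Fixed sites | 1.631 | 4.93 | 34% | 37% | 19% | 4.6 |

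**5. Sensitivity.**
- Linear time instead of epoch categories: design effect 2.79 (ICC 0) to 4.71 (fixed sites), power 54% to 35% for 2.52 points.
- Adjustment for baseline HADS (variance × (1 − 0.5²)/(2 × (1 − 0.5)) = 0.75), epoch categories: power 63% at ICC 0, 48% at ICC 0.05, 43% with fixed sites.
- Both favourable choices together (linear time, baseline adjustment, ICC 0): 66% for 2.52 points and 71% for 2.67.
- Within-site correlation that decays between epochs (cluster autocorrelation 0.8, ICC 0.05): design effect 5.0 to 5.7, power 33% to 30%.
- No time adjustment: design effect 1.0 to 1.18 with random sites at ICC 0 to 0.05, and 1.29 with fixed sites. Only here is 1.5 enough.

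**The case against.** The best reply is that the range is tighter than the article permits. Alpha is not given. Time is to be accounted for, but not necessarily by seven categories. Case-mix adjustment is planned, and if it includes baseline HADS, power rises to 48–63% with random sites at ICC 0 to 0.05. The lowest figure, 34%, needs fixed site effects, whereas a hierarchical model suggests random ones, for which power stays at about 38% or above in the range tested. Also, the factor of 3.0 is measured against an uninflated trial. The plan already budgets 1.5, so the uncovered shortfall is 3.0/1.5 = 2.0-fold at ICC 0 and 4.29/1.5 = 2.9-fold at ICC 0.05. Finally, the authors say openly that they had no ICC data.

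The points about the range stand as qualifications: the exact power depends on modelling choices that the article leaves open. They do not rescue the claim, because no time-adjusted variant examined reaches 80%; the most favourable gives 66% for 2.52 points. The primary outcome is defined and sized as a change score, and baseline HADS is not named as a covariate. The admission about the ICC concerns clustering and does not touch the loss from time adjustment, which is there at ICC 0.

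**Conclusion.** The concern holds. The arithmetic from 200 per group to 600 is correct, but the multiplier is the wrong one for this design and this analysis. For change scores with epoch and site adjustment, the design effect is 3.0 to 4.9 and power is 51% down to 34% for the difference the plan sized for. With random sites only, the range is 51% to 38%. The difference detectable with 80% power is 3.6 to 4.6 points, or 20–26% of 17.8, which lies outside the stated 10–15%.

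These figures rest on the assumptions listed with the calculation. Dropout, small-sample inference with five clusters, or correlation that decays over time would lower power further; baseline adjustment would raise it, though not to 80%. The threefold loss at ICC 0 follows from the Table 1 layout and epoch adjustment alone.

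**What to change.** Replace the sentence on the 1.5 design effect with the cross-sectional stepped-wedge variance for the actual layout: five sites, seven epochs, empty Training cells, 20 patients per cell, fixed epoch effects, and a stated ICC range such as 0 to 0.05. State alpha and sidedness.

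Then restate what 600 patients can do. With random sites, power is about 38–51% for 2.5 points; equivalently, the difference detectable with 80% power is about 3.6 to 4.3 points. If baseline HADS is made a covariate in the primary model, the detectable difference is about 3.1 to 3.7 points, and the plan should then say so. Keep the 600 patients and commit to interpreting the primary result by its confidence interval, so that a non-significant finding is not read as absence of effect.

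The cost is one re-run calculation and one reworded paragraph. No extra patients are needed, but the stated power becomes less favourable. Restoring 80% by enlarging cells would be a different matter: even at ICC 0 it would need about 400 × 3.0 = 1,200 patients.
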